#### Sample size calculation

Assuming an alpha of 0.05 and a beta of 0.90, an improvement in perceived daily functioning (defined as a score less than or equal to 4 on the Daily Functioning Thermometer (DFT), our primary outcome) at T12 occurring in 20% of the patients in the intervention group versus 5% of those in the control group requires at least a net number of 116 patients per arm (N = 232; 5 patients per practice nurse). It will be necessary to take account of a possible dependence between observations on patients of the same practice nurse. The intra-class correlation coefficient (ICC) is assumed to be 0.04, a median value for cluster-RCTs in the primary care setting [33]. Assuming a 30% loss to follow-up [17] we need to recruit at least 331 patients (8 per PN). Since participation in the screening procedure will not necessarily mean that patients also give informed consent for the effect evaluation, 10 consecutive patients for each PN will be invited to participate in the effect evaluation (N = 460).

#### Patient recruitment

All patients with a clinically established diagnosis of type 2 diabetes mellitus who are able to read and write Dutch will be sent a letter by their GP, explaining SMS and asking for informed consent to participate. Patients will receive this letter six weeks before a planned diabetes consultation with their PN. The enclosed screening questionnaire will contain the same instruments that PNs in the intervention group are going to use to detect whether patients are eligible for the self-management support, i.e. the ‘Daily Functioning Thermometer’ (DFT) and the 3-item Distress Screener (DS) [22]. For more information about these instruments, see the section on Measurements below. Patients will be asked to return the completed questionnaire to the research centre and give informed consent for their data to be used for recruitment if they are found to be at risk. For each practice nurse, 10 consecutive patients with scores of DFT >4 and DS >3 will be asked to participate in the study and to give informed consent for the follow-up measurements. To prevent bias, PNs will not be notified about the outcomes of the recruitment procedure.

A flowchart of the trial is shown in Figure 2.

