### Clinical effect evaluation

#### Design

The effect evaluation of SMS involves a pragmatic 2-armed cluster-randomised controlled trial (cluster-RCT) with PNs as the unit of randomisation. Allocation concealment will be achieved by having an independent experienced research assistant perform a blockwise randomisation using a random number seed computer program. PNs (n = 46) will be assigned to an intervention group or control group at an allocation ratio of 1:1, after stratification into PNs working alone in a practice, PNs working in a team and PNs working in different practices. PNs working in the same general practice will be randomised to the same trial arm.

PNs in the intervention arm will be trained to apply SMS in addition to the usual care, which consists of 3-monthly diabetes check-ups according to the current guidelines [10]. PNs in the control arm will be instructed to provide usual care.

Patients with emotional distress and problems of daily functioning will be included in the effect evaluation. To maintain the balance between the intervention and control groups, a screening procedure will be carried out by the research centre. A self-administered postal questionnaire will be used to detect eligible patients.

Approval for this study has been obtained from the Medical Ethics Committee of Maastricht University/University Hospital Maastricht.

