#### Measurements

To assess the effectiveness of SMS, follow-up measurements will be carried out at baseline and 4 and 12 months after inclusion. Table 3 provides an overview of the measures of the effect evaluation and the times of assessment.

**Table 3 T3:** Effect evaluation: outcome measures and time of assessment

**Concept**	**Measurement**	**Items**	**Moment in time**			
			**3-monthly diabetes consultations during follow-up**	**T0**	**T-4**	**T-12**
*Primary outcome*						
Daily functioning	DFT	1		*	*	***
*Secondary outcomes*						
Diabetes-related emotional distress	PAID	20		*	*	***
Mental health problems	PSYCHLOPS	9	*^2^	*^1^	*	***
	4DSQ	50			*	*
Quality of life	SF-12	12		*	*	***
Participation and autonomy	IPA	32 + 9		*	*	***
Job performance	SF-HLQ	5		*	*	*
Self-management knowledge and behaviour	PIH-NL	12		*	*	***
General self-efficacy	GSES-12	12		*	*	*
Control over the disease	Average blood glucose level (HbA1c)	1	*			
Health care use		5		*	*	*
*Covariates*						
Patient demographics	Sex	1		*		
	Age	1		*		
	Year of diagnosis	1		*		
	Treatment of diabetes	1		*		
	Marital status	1		*		
	Education	1		*		
Practice nurse demographics	Age	1		*		
	Training	1		*		
	Type of general practice(s) (one GP, two GPs, group, health centre)	1		*		

1 Only patients in intervention arm. Risk of contamination.

2 Only eligible patients (Distress Screener > 3).

* = measuring moment.

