##### Secondary outcome measures

Three instruments will assess patients’ emotional health status.

Diabetes-related emotional distress will be measured by means of the Problem Areas in Diabetes questionnaire (PAID). This 20-item scale (with five-point Likert scales) describes common problematic situations for diabetes patients, each representing a unique area of diabetes-specific emotional distress. The sum of the scores for the 20 items is multiplied by 1.25 to get a final score between 0 and 100. The Dutch PAID has good internal consistency and validity [35-37].

The Four-Dimensional Symptom Questionnaire (4DSQ) will be used to measure the presence and severity of mental health problems [23]. The levels of distress (16 items), depression (6 items), anxiety (12 items) and somatisation (16 items) will be assessed. The reference period is ‘the past week’. The item scores are summated to obtain scale scores. The 4DSQ has been found to be a valid self-reported questionnaire in the primary care setting [23]. For a more qualitative evaluation of emotional problems that patients experience, we will use the Psychological Outcome Profiles (PSYCHLOPS). The PSYCHLOPS asks patients to describe and score their own emotional health problems. It is a validated patient-generated measure with pre-therapy, during-therapy and post-therapy versions. The instrument is intended to measure individual changes. It is responsive to change and is internally consistent [38].

Both PSYCHLOPS and 4DSQ explicitly expect patients to define and rate their emotional health problems. An increased awareness about their emotional problems of daily functioning could influence the issues discussed during the diabetes consultation, which could result in reduced contrast between the two groups. We will not use the 4DSQ and the PSYCHLOPS in the control group at T0, as the timing of the baseline measurement is just before a diabetes consultation, whereas the assessment at T4 is further removed from a diabetes consultation. Inclusion of the PSYCHLOPS and 4DSQ at both T4 and at the end of the follow-up period (T12) will provide insight into individual changes. In the intervention group, inclusion of the PSYCHLOPS at baseline will provide valuable information about the patients’ individual emotional problems. The 4DSQ does not need to be included in the baseline measurement as it is already part of the SMS intervention.

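### Patients consent and complete T0 after their practice nurse has been allocated, the T0 set differs by arm, and the stated protections do not cover arm-dependent consent or T0 return

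*Protocol article*

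**What the plan says.** The Design section of the clinical effect evaluation describes a "pragmatic 2-armed cluster-randomised controlled trial (cluster-RCT) with PNs as the unit of randomisation". On concealment it states: "Allocation concealment will be achieved by having an independent experienced research assistant perform a blockwise randomisation". It adds one measure aimed at comparability of the arms: "To maintain the balance between the intervention and control groups, a screening procedure will be carried out by the research centre".

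Under Patient recruitment, patients with type 2 diabetes "will be sent a letter by their GP, explaining SMS and asking for informed consent to participate", six weeks before a planned consultation. The enclosed screener holds the DFT and the DS. For each nurse, ten consecutive patients with DFT above 4 and DS above 3 are asked for a second consent, covering the follow-up measurements. The section closes with "To prevent bias, PNs will not be notified about the outcomes of the recruitment procedure".

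The baseline set is not the same in the two arms. The footnote to PSYCHLOPS at T0 in Table 3 (Measurements) reads "Only patients in intervention arm. Risk of contamination". Secondary outcome measures gives the reason: PSYCHLOPS might prompt control patients to raise emotional problems at the coming check-up. It continues: "In the intervention group, inclusion of the PSYCHLOPS at baseline will provide valuable information".

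The Discussion subsection on methodological challenges describes the postal screening as finding eligible patients in both arms, and requires that it leave care in the control arm undisturbed. The data analysis section gives age, sex and socio-economic status, and nurse age and education, as examples of covariates. It does not name screening DFT or DS.

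**The concern.** Randomising nurses balances nurses and, on average, their whole patient lists. It does not balance the subset of patients who agree to join once the arms exist. If willingness to consent or to return T0 depends on arm, the two groups can differ before SMS has had any effect.

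The primary outcome in the sample size section is a DFT of 4 or less at T12 among patients who entered with DFT above 4. Entry score and distress plausibly predict who crosses that line. An arm difference in who joins could therefore move the responder rate without a treatment effect, and the covariates named would remove only part of it.

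**Working it through.** **Order of events**

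1. T0: certain. PSYCHLOPS cannot be sent at T0 to one arm only unless the arm is known when T0 is sent.
2. Invitation and consent: strongly implied. The Discussion describes screening in arms that already exist. The letter goes out six weeks before a consultation in which intervention nurses are to apply SMS, for which they must already have been allocated and trained. No text places recruitment before randomisation. The trial flowchart (Figure 2) is not available to check.

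**What each stated safeguard covers**

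| Safeguard | Where | Acts on | Acts on consent or T0 return? |
|---|---|---|---|
| Concealed draw of nurse allocations | Design | which arm a nurse enters | No |
| Central screening, common cut-offs, consecutive patients | Design; Patient recruitment | who is identified and invited | No |
| Nurses not told who was recruited | Patient recruitment | how nurses treat recruited patients | No |

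**The plan's own figures** (Sample size calculation: 20% v 5%, alpha 0.05 taken as two-sided, stated beta of 0.90 read as power, ICC 0.04, 5 patients per nurse)

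- Per arm, unclustered: [1.960·√(2·0.125·0.875) + 1.282·√(0.20·0.80 + 0.05·0.95)]² / 0.15² = 100.1.
- Design effect: 1 + (5 − 1)·0.04 = 1.16, and 100.1 × 1.16 = 116. The stated 116 per arm is reproduced.
- Loss to follow-up: 232 / 0.70 = 331.4. The stated 331 is reproduced, to rounding.

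**Room for selective consent**

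331 / 460 = 0.72. The recruitment target is met with 72% consent, so up to 28% of those invited may decline.

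**Illustration (the prognosis and consent splits are assumptions)**

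Suppose half of the invited patients have a better and half a poorer prognosis, averaging the plan's 5% responders with no treatment effect. In the control arm both halves consent at 72%. In the intervention arm consent differs by half but still averages 72%. The intervention-arm rate without any effect of SMS is then

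(better rate × better consent + poorer rate × poorer consent) / (better consent + poorer consent).

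The chance of a significant result uses a two-sided 5% normal approximation with 116 / 1.16 = 100 effective patients per arm.

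| Responders, better / poorer half | Intervention consent, better / poorer half | Rate without effect, intervention v control | Spurious difference | Chance of significance |
|---|---|---|---|---|
| 8% / 2% | 80% / 64% | 5.3% v 5% | 0.3 points | 5.1% |
| 8% / 2% | 90% / 54% | 5.75% v 5% | 0.75 points | 5.6% |
| 10% / 0% | 80% / 64% | 5.6% v 5% | 0.6 points | 5.4% |
| 10% / 0% | 90% / 54% | 6.25% v 5% | 1.25 points | 6.7% |

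First row: (0.08·0.80 + 0.02·0.64) / 1.44 = 0.0533. Last row: (0.10·0.90 + 0 × 0.54) / 1.44 = 0.0625. Against the planned difference of 15 points these shifts are small.

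**The case against.** The best defence is that selection is largely by rule. The research centre screens with the same instruments and cut-offs in both arms and takes consecutive patients, so staff have little discretion. That stands: selective identification is well controlled, and what remains is the patient's own choice.

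Second, the article describes one letter to all patients and nowhere says that patients know their arm. A reader might infer that the staff who invite patients are unmasked, or that patients are told their allocation. The text does not support this; it is silent. A condensed article may also leave such operational detail to the full protocol. Silence does not establish a fault, but the arm-specific T0 set is stated, and it is enough to show that baseline collection depends on arm.

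Third, PSYCHLOPS is 9 items on top of 108 outcome items that both arms receive at T0 (1 + 20 + 12 + 41 + 5 + 12 + 12 + 5), about 8% more. Both arms already answer the 20-item PAID on emotional distress, and the article does not say that the booklet accompanies the consent request. So the booklet is a weak lever on T0 return and a speculative one on consent. The anti-contamination reason for withholding PSYCHLOPS from controls is also sound. It does not require PSYCHLOPS to travel with T0 in the other arm.

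Fourth, the covariate list is introduced by way of example and changes in outcome are to be analysed, so baseline DFT is not ignored. This stands in part. A change score uses baseline DFT for the continuous outcome, but the proportion at DFT 4 or below does not.

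**Conclusion.** The point holds as a moderate design weakness. Allocation precedes T0 for certain and precedes invitation and consent by strong implication. None of the stated safeguards reaches arm-dependent consent or T0 return. It is a risk, not a demonstrated imbalance, and its size cannot be derived from the document. Under the assumed consent patterns the false-positive rate is about 5% to 7%, and the upper end needs 90% v 54% consent by prognosis within one arm.

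Two stronger readings should be resisted. A reader might posit untreated rates of 7% to 10% against 5% and conclude that false positives are common. No consent pattern examined here gives more than 6.3%, and nothing in the document supports the larger values. A reader might also suppose that patients sit just above the cut-off, so that slight selection tips many across. Entry is any DFT above 4 on a 0 to 10 scale, and the plan itself expects only 5% of controls to cross.

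**What to change.** 1. Send both arms the same invitation and the same T0 booklet. Collect the intervention-only PSYCHLOPS separately, after T0 is returned and before the consultation. Controls still do not see it at baseline, so the protection against contamination is kept. Cost: one extra mailing step in one arm and slightly later collection of that instrument.
2. Adjust the primary multilevel model for screening DFT and screening DS. Both are collected identically in both arms before the second consent, so no new data are needed. This removes imbalance in those scores, but not in unmeasured motivation.

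Where feasible, also send invitations from coded nurse lists without the arm shown, and report numbers invited, consented and returning T0 by arm, so that readers can judge whether selection occurred. Randomisation, training and sample size stay as they are.

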**Figure 2 F2:**
[figure not shown]
**Flowchart for SMS trial.** * DFT = Daily Functioning Thermometer. ** DS = Distress Screener.

#### Measurements

To assess the effectiveness of SMS, follow-up measurements will be carried out at baseline and 4 and 12 months after inclusion. Table 3 provides an overview of the measures of the effect evaluation and the times of assessment.

**Table 3 T3:** Effect evaluation: outcome measures and time of assessment

**Concept**	**Measurement**	**Items**	**Moment in time**			
			**3-monthly diabetes consultations during follow-up**	**T0**	**T-4**	**T-12**
*Primary outcome*						
Daily functioning	DFT	1		*	*	***
*Secondary outcomes*						
Diabetes-related emotional distress	PAID	20		*	*	***
Mental health problems	PSYCHLOPS	9	*^2^	*^1^	*	***
	4DSQ	50			*	*
Quality of life	SF-12	12		*	*	***
Participation and autonomy	IPA	32 + 9		*	*	***
Job performance	SF-HLQ	5		*	*	*
Self-management knowledge and behaviour	PIH-NL	12		*	*	***
General self-efficacy	GSES-12	12		*	*	*
Control over the disease	Average blood glucose level (HbA1c)	1	*			
Health care use		5		*	*	*
*Covariates*						
Patient demographics	Sex	1		*		
	Age	1		*		
	Year of diagnosis	1		*		
	Treatment of diabetes	1		*		
	Marital status	1		*		
	Education	1		*		
Practice nurse demographics	Age	1		*		
	Training	1		*		
	Type of general practice(s) (one GP, two GPs, group, health centre)	1		*		

1 Only patients in intervention arm. Risk of contamination.

2 Only eligible patients (Distress Screener > 3).

* = measuring moment.

##### Background variables

Patient variables that will be reported are sex, age, year of diagnosis, treatment of diabetes (insulin therapy or tablets), marital status and education. Furthermore, we will record the age of the PNs, the number of PNs for diabetes management working in a general practice, as well as the educational background of the PNs.

##### Primary outcome measure

The primary outcome will be daily functioning as measured by means of the Daily Functioning Thermometer (DFT). This is a visual analogue scale (VAS) on which patients can rate the overall burden of diabetes on their daily functioning by indicating a position along a continuous vertical 100 mm line between 0 (‘no burden at all’) and 10 (‘extreme burden’). The VAS score is determined by measuring the distance to the point marked by the patient, in millimetres. The DFT is comparable to the Distress Thermometer (DT), an easily understood, valid and feasible self-report measure of distress used among various groups of cancer patients [34]. A cut-off score of 4 has been chosen to differentiate between patients who could benefit from self-management support by the PN (DFT > 4) and patients who have apparently found a satisfactory way to live with the consequences of their diabetes (DFT ≤ 4). A pilot study among 7 patients with type 2 diabetes mellitus confirmed the face validity of the DFT.

##### Secondary outcome measures

Three instruments will assess patients’ emotional health status.

Diabetes-related emotional distress will be measured by means of the Problem Areas in Diabetes questionnaire (PAID). This 20-item scale (with five-point Likert scales) describes common problematic situations for diabetes patients, each representing a unique area of diabetes-specific emotional distress. The sum of the scores for the 20 items is multiplied by 1.25 to get a final score between 0 and 100. The Dutch PAID has good internal consistency and validity [35-37].

The Four-Dimensional Symptom Questionnaire (4DSQ) will be used to measure the presence and severity of mental health problems [23]. The levels of distress (16 items), depression (6 items), anxiety (12 items) and somatisation (16 items) will be assessed. The reference period is ‘the past week’. The item scores are summated to obtain scale scores. The 4DSQ has been found to be a valid self-reported questionnaire in the primary care setting [23]. For a more qualitative evaluation of emotional problems that patients experience, we will use the Psychological Outcome Profiles (PSYCHLOPS). The PSYCHLOPS asks patients to describe and score their own emotional health problems. It is a validated patient-generated measure with pre-therapy, during-therapy and post-therapy versions. The instrument is intended to measure individual changes. It is responsive to change and is internally consistent [38].

Both PSYCHLOPS and 4DSQ explicitly expect patients to define and rate their emotional health problems. An increased awareness about their emotional problems of daily functioning could influence the issues discussed during the diabetes consultation, which could result in reduced contrast between the two groups. We will not use the 4DSQ and the PSYCHLOPS in the control group at T0, as the timing of the baseline measurement is just before a diabetes consultation, whereas the assessment at T4 is further removed from a diabetes consultation. Inclusion of the PSYCHLOPS and 4DSQ at both T4 and at the end of the follow-up period (T12) will provide insight into individual changes. In the intervention group, inclusion of the PSYCHLOPS at baseline will provide valuable information about the patients’ individual emotional problems. The 4DSQ does not need to be included in the baseline measurement as it is already part of the SMS intervention.

Quality of life, i.e. functional health and well-being from the patient’s point of view, will be measured by means of the 12-item Short-Form Health Survey (SF-12), a validated subset of the generic health status questionnaire SF-36 [39,40]. Data will be summarised in 2 scales: a physical component summary (PCS) and a mental component summary (MCS).

Participation and autonomy will be measured by means of the Impact on Participation and Autonomy (IPA) questionnaire. The IPA has proved to be valid, reliable and responsive to change [41]. Thirty-two items (five-point Likert scales) cover five domains of participation: ‘autonomy indoors’, ‘family role’, ‘autonomy outdoors’, ‘social life and relationships’ and ‘work and education’. A score for each subscale will be calculated. In addition, 9 items will evaluate the extent to which limitations are experienced as problematic: ‘no problems’, ‘minor problems’ or ‘major problems’. These items will be scored separately [42].

Five items from the Short-Form Health and Labour Questionnaire (SF-HLQ) will be used to measure difficulties of job performance due to health problems. The SF-HLQ is a generic and validated measurement to collect data about productivity loss relating to health problems [43].

Patients’ self-management knowledge and behaviours regarding their diabetes will be measured by the Partners in Health (PIH) scale [44]. This scale reliably and validly measures aspects of patient progress within a self-management programme for a chronic condition. We will use the Dutch version (PIH-NL). The 12 items (0–8 Likert scales with 0 indicating high self-management and 8 low self-management) cover four domains of patients’ competency in relation to the self-management of their chronic condition (knowledge, coping, management of condition and adherence to treatment).

The General Self-Efficacy Scale (GSES-12) will be used to assess the patients’ belief in their ability to organise and engage in certain behaviours. The sum score of the 12 items (five-point Likert scales) reflects an internally consistent and stable unidimensional construct of general self-efficacy [45,46].

At each diabetes consultation, the blood glucose level over the past 2 to 3 months (HbA1c) will be measured and recorded in the registration system.

The effect of SMS on patients’ health care utilisation refers to individual numbers of visits to the general practice, specialist referrals and admissions, mental health care consultations, use of home care and hours of paid and unpaid household help. Patients will record their health care use retrospectively (over the last month) in the patient questionnaires administered at baseline and after 4 and 12 months. Data about referrals to the GP, and the number of contacts with the general practice will be collected from the GP’s registration system.

